# Nebulized versus intravenous morphine titration for the initial treatment of severe acute pain in the emergency department: study protocol for a multicenter, prospective randomized and controlled trial, CLIN-AEROMORPH

**DOI:** 10.1186/s13063-019-3326-3

**Published:** 2019-04-11

**Keywords:** Morphine, Pain, Analgesia, Nebulized, Randomised controlled trial, Single blind

## Abstract

**Background:**

Intravenous morphine titration (IVMT) is the French gold standard for opioid treatment in the emergency department (ED). Nebulized morphine titration (NMT) may represent an alternative without venous access, but it has not been adequately studied in adults. We test the hypothesis that NMT is at least as effective as IVMT to initially manage severe acute pain in the ED.

**Methods/design:**

We designed a multicenter (10 French EDs), single-blind, randomized and controlled trial. Adults between 18 and 75 years with visual analog scale (VAS) ≥ 70/100 or numeric rating scale (NRS) ≥ 7/10 will be enrolled. We will randomize 850 patients into two groups to compare two routes of MT as long as VAS >  30 or NRS >  3. In group A (425), patients will receive an initial NMT for 5–25 min associated with titration of an intravenously (IV) administered placebo of physiologic serum (PS). In group B (425), patients will receive IVMT plus nebulized PS placebo.

NMT is defined as a minimum of 1 and a maximum of 3 5-min nebulized boluses of 10 mg or 15 mg (weight ≥ 60 kg), at 10-min fixed intervals. IVMT is defined as a minimum of 1 and a maximum of 6 boluses of 2 mg or 3 mg (weight ≥ 60 kg), at 5-min fixed intervals. Nebulized placebo titration will be performed every 10 min. IV titration of PS will be performed every 5 min. In both groups, after 25 min, if VAS > 30/100 or NRS > 3/10, routine IVMT will be continued until pain relief.

Pain severity, vital signs, bronchospasm, and Ramsay score will be recorded every 5 min. The primary outcome is the rate of relief obtained 1 h from the start of drug administration. Complete pain relief in both groups will be compared with a non-inferiority design. Secondary outcomes are pain relief at 30 min (the end of NMT) and at 2 h and median pain relief. We will compare final doses, and study the feasibility and tolerance of NMT (protocol deviations, respiratory or hemodynamic depression, sedation, and minor vegetative side effects). Co-analgesia will be recorded. Discharge criteria from the ED and hospital are defined.

**Discussion:**

This trial is the first multicenter randomized and controlled NMT protocol for severe pain in the ED using the titration concept. We propose an original approach of combined titration with an endpoint at 1 h and a non-inferiority design.

**Trial registration:**

ClinicalTrials.gov, NCT03257319. Registered on 22 August 2017.

**Electronic supplementary material:**

The online version of this article (10.1186/s13063-019-3326-3) contains supplementary material, which is available to authorized users.

## Background

The treatment of severe acute pain in the emergency department (ED) has been a public health priority in France for several years [1–4]. Spontaneous pain is the primary reason for ED consultation, whatever the etiology [3]. Severe pain in the ED is defined by a visual analog scale (VAS) ≥ 60/100 or numeric rating scale (NRS) ≥ 6/10, and the French consensus conference on the subject [5–7] recommends emergency administration of intravenous morphine titration (IVMT) for pain relief. Morphine boluses of 2 or 3 mg can be administered every 5 min until relief is obtained (VAS ≤ 30 or NRS ≤ 3) [8–12]. Many studies have shown the safety and benefit of IVMT [13–16]; in particular, this approach has the advantage of being ubiquitous, while offering support for the concept of individualized dose-limiting side effects. The large intervariation and intravariation of the morphine molecule is thus taken into account, contrary to when dose-weight posology is administered. Side effects are known to be rare with IVMT: Respiratory depression associated with morphine is uncommon (or nil), and minor side effects do not exceed 10–15% [11, 12]. Other routes of morphine administration, titrated or not (oral, subcutaneous), do not allow such rapid relief, are not easy to handle safely, and are actually reserved for long-term treatment [5–9]. IVMT has become the standard morphine titration protocol in French EDs in cases of spontaneous severe acute pain [5–7].

Despite legal provisions and learned society recommendations, IVMT remains insufficiently applied or applied with delays [17]. The availability of morphine is good (low direct costs, low indirect costs of nursing administration and educational intervention), but the real requirements of opioids are still too limited, and oligoanalgesia persists in many countries [18–20]. Moreover, deviations from recommended protocols are frequent; i.e., additional doses are administered at abnormally long intervals between boluses and discontinued at an early stage [12]. Organizational causative factors are numerous, including the high workload especially in overcrowded EDs (significant flow of patients): there are restrictive legal conditions of deliverance as well as rigidity of application with the burden of implementation, and this method is particularly time-consuming for nurses. The need for rapid venous access is also negatively involved. It is difficult to dissociate blood sample tests for diagnosis purposes and venous therapeutic access for analgesia. To save time and to avoid a second puncture, nurses may wait for all prescriptions before setting up the venous access. Moreover, IV access is algogenic in itself, linked to added risk of infection and decreased mobility in the ED particularly in ambulatory patients. Nebulized opiates without venous access might represent another route of administration, providing management of opiates in cases of severe pain that could be practical for sites with limited means (prehospital as an inpatient) or sites that are maintained in substandard conditions.

However, data on the pain management of adults using a nebulized route in the ED are scarce. The majority of clinical studies involve patients in long-stay medical departments who have dyspnea and not pain (cancer or chronic respiratory insufficiency [21–26]). Some work has been carried out in pediatric EDs [27] or only in trauma patients [28–30]. Some protocols have tested inhaled morphine hydrochloride, and others fentanyl [27, 31]. Aerosol techniques vary from one study to another (intranasal administration, facial nebulization) as well as posology and pain intensity at inclusion (i.e., moderate and severe pain tested simultaneously). Criteria and time to pain assessment seem to be determined empirically (complete relief for patients, 50% reduction in pain intensity, etc.). Moreover, analysis of the literature shows that previous protocols involving nebulized morphine for pain relief in the ED aimed to evaluate a weight-associated “loading dose” rather than a morphine titration protocol. For example, a recent study tested an emergency dose of 0.2 mg/kg of morphine, unsuccessfully [28]. Although morphine is probably absorbed via the ear-nose-throat and bronchopulmonary systems, the variability of the pharmacodynamic effects of morphine for the same plasma concentration is unlikely to be modified [32–34] and remains a central parameter. Nebulized morphine titration (NMT) could be the alternative to IVMT (current reference treatment) with the same objectives, ensuring the most standardized and reproducible route of administration and the easiest method of controlling bioavailability and maintaining safety conditions in the ED. One study published in 2015 included 300 young trauma patients in the ED with the aim of testing two protocols of NMT, with two different bolus doses of morphine for repeated administration every 10 min [30]. In reality, the small number of boluses reported (1 is the median value for the highest dose versus 2 for the lowest dose) questions the morphine titration concept. In brief, the principle of morphine titration is most often forgotten or betrayed in the opioid nebulization protocols proposed in the literature, and comparative clinical trials with IVMT protocols are rare.

Pharmacokinetic data are also insufficient, even in healthy volunteers. Some data in healthy volunteers without any pain stimulus are available, but the results are not consistent and dyspnea seems to have been the priority area of research [35–40]. The nebulization durations are arbitrary, resulting in great variability in the kinetics of absorption of opiates tested and studies that are difficult to compare. The bioavailability measured varies from 8 to 59%, and the delay of the peak effect ranges from 0 to 10 min, sometimes comparable and sometimes preferable to oral administration. Absorption is sometimes described as an exponential model and sometimes as an inverse curve with immediate absorption between 50 and 75%. Some studies have attempted to specifically determine the links between the pharmacokinetics of opiates and the size of aerosolized particles [37, 38, 40–43] and/or the aerosol material, but the exact bioavailability of a morphine hydrochloride aerosol based on a nebulization system routinely used in a hospital wall socket remains poorly studied.

Considering the results reported in the literature and clinical practice, many questions remain before switching from IVMT to NMT. No simple conversion can be made between the 3-mg or 2-mg intravenous bolus, which is the reference for titration, and bolus doses to be nebulized. No preliminary study has determined which optimized and standardized dose of nebulized bolus could be repeated to achieve complete pain relief in patients and ensure safety and tolerance. The ideal times of the aerosol bolus and between each aerosol bolus have not been tested yet and cannot be deduced from what is proposed intravenously. Some clinical studies have tended to show relief, especially at the beginning of nebulization, in the first 5 min (when measured), and others have shown a greater rapidity of appearance of metabolites of morphine in the blood than in other routes of administration but without studying pain relief parallelism [27, 28, 35, 36]. Again, the data are insufficient and deserve to be completed.

In the absence of sufficiently robust data, further research on pain in healthy volunteers appears to be an essential prerequisite for a clinical trial on major emergencies. We performed AEROMORPH1 (EUDRACT 2013-001977-26, results in submission process) in order to determine, within a nebulized morphine protocol in healthy volunteers with pain (phase I trial), the pharmacokinetic characteristics and the feasibility of a single 5-min nebulized safety bolus of morphine which could be tested and repeated in the ED.

Given the AEROMORPH1 preliminary data and taking into account the poor results in the literature, we decided to propose the initiation of morphine titration by a new route of administration rather than exclusive NMT. We aim to test the hypothesis that a combined method of morphine titration, initiated by a maximum of 3 nebulized boluses, is at least as effective as IVMT performed exclusively according to the reference protocol for the treatment of patients with severe spontaneous pain (VAS between 70 and 100 mm or NRS ≥ 7/10) in the ED. We decided to perform a multicenter, randomized, placebo-controlled study, a methodological design associated with the highest level of evidence.

## Methods/design

### Study aims

The aim of our study is to evaluate two different methods of analgesia by morphine titration for the management of severe acute pain in the ED. First we will compare a combined morphine titration started by NMT and then IVMT, and second the reference route of administration of morphine titration, i.e., exclusive IVMT.

The primary outcome is to assess whether the two methods are as effective to provide pain relief at 1 h from the beginning of morphine titration.

Secondary outcomes are first, to compare for each titration method all the parameters of analgesic efficacy, second to assess the feasibility of this new method of combined morphine titration, and third to evaluate the tolerance of the nebulized route of morphine administration.

### Study design

#### Setting

The CLIN-AEROMORPH trial is a multicenter, prospective, randomized, double-dummy, placebo-controlled trial conducted in 10 French adult EDs in tertiary care academic hospitals, with more than 30,000 patient visits per year. All these centers manage more than 2500 patients with severe pain per year routinely using IVMT according to French recommendations and have already participated in randomized controlled trials. Rouen University Hospital’s adult ED will coordinate the study and handle the data analysis. The coordinating investigator of this center and of the whole study has conducted large trials on IVMT before [12]. The trial will be conducted in the flow of routine patient care. A single-blinding design was the only possibility: Blinding may not be complete because of the aerosol preparation by nurses and physicians. The CLIN-AEROMORPH study design and flow chart are provided in Fig. 1.

**Fig. 1 Fig1:**
[figure not shown]
CLIN-AEROMORPH study flow chart

#### Subject selection and inclusion criteria

Criteria for eligibility are adult patients, 18–75 years of age, presenting to the ED with a primary complaint of spontaneous severe acute pain who are being considered for admission to the ED observation unit whatever their pain etiology. An episode of severe pain is defined as the occurrence of pain that is rated 70/100 or more on the VAS (0–100), and when the VAS evaluation is impossible, pain that is rated 7/10 or more on the NRS (0–10). The VAS handheld slide rule will be shown and explained to the patients. When patients have difficulties in manipulating the VAS slide rule, nurses will be allowed to use the NRS (from 0 to 10), as these two scales are equivalent in the ED [5]. All nurses in the ED have been trained to assess pain using these unidimensional scales. A second VAS or NRS measurement will be taken in the examination room, to confirm the first measurement of severe acute pain recorded in the ED. If this second measurement confirms VAS ≥ 70/100 or NRS ≥ 7/10, the investigator will check the inclusion and exclusion criteria for enrollment.

Patients will be screened consecutively 5 days per week (Monday to Friday) during the day, when the organizational conditions for enrollment are met, until the sample size of 850 patients is reached. Patients cannot be consecutively enrolled in the study because high inflow or high workload in participating EDs is an obstacle, and is difficult to predict. Patients will be included when the study coordinator or a dedicated team member is available for enrollment and when a single examination room is available for treatment.

Inclusion and exclusion criteria are presented in Table 1.

**Table 1 Tab1:** Inclusion and exclusion criteria

Inclusion criteria	
• Age ≥ 18 and < 75 years	
• VAS ≥ 70/100 or NRS ≥ 7/10	
• Patient affiliated with or beneficiary of a social security category	
• For women (childbearing age)	
○ Effective contraception (oral contraception, intrauterine device or use of condoms)	
○ Menopausal status (amenorrhea less than 12 months before the inclusion visit)	
○ Objectivized sterility (diagnosis or surgically)	
Exclusion criteria	
• Chronic pain (> 3 months)	
• Taking opioids more than 10 days (including opioids as tramadol and/or codeine)	
• Taking opioids in the emergency room within 4 h	
• Taking rifampicin	
• Impaired ability to discern, cognitive impairment	
• Morphine-related contraindications	
○ Chronic obstructive or restrictive respiratory failure known or suspected, compensated or not	
○ Hypersensitivity to the active substance or to any of the excipients	
○ Severe hepatocellular insufficiency (known or suspected)	
○ Chronic renal failure known or suspected	
○ Acute renal failure (creatinine clearance < 60 ml/min/1.73 m^2^ and/or increase of 25% from baseline)	
○ Uncontrolled epilepsy	
○ Cranial trauma (intracranial hypertension)	
○ Associations with buprenorphine, nalbuphine, pentazocine, or naltrexone	
• Active drug history or practice(s)	
• Obvious need to reduce fracture or dislocation in the emergency room	
• Suspected occlusive syndrome	
• SpO2 < 95%	
• Respiratory rate (RR) < 12 breaths/min	
• Glasgow Coma Scale (GCS) < 15 or other alertness disorders	
• Heart rate (HR) < 50 bpm and/or auriculo-ventricular block (PR interval > 200 ms)	
• Arterial hypotension with systolic blood pressure TA syst < 100 mmHg	
• Pregnancy or lactation	
• Persons deprived of their liberty by an administrative or judicial decision, persons placed under the safeguard of justice, guardianship	
• Patients with poor comprehension of spoken or written French	
• Patients participating in another interventional clinical study	
• Contraindication related to the use of saline solution	
• Contraindications related to the use of aerosol:	
○ Necessity to access the face	
○ Allergy known to plastic	
○ Claustrophobia	

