### Safety reporting

All AEs that occur during the study period observed by one of the clinical staff, or reported by the patient or parent/guardian spontaneously or in response to a direct question, will be noted on appropriate forms, i.e., for AEs, serious adverse events (SAEs), or suspected unexpected serious adverse (drug) reactions (SUSARs). AEs will be classified on the form in terms of their severity, association with the study drug, expectedness, and seriousness. They will be recorded on an AE log. AEs will be reported to the sponsor as soon as possible and on a yearly basis as part of an annual safety report and at the end of the trial. The sponsor (CHU-Hôpitaux de Rouen/Rouen University Hospital, Department of Research and Innovation) has the responsibility to ensure all relevant and available information is forwarded to the competent authority (Irish Medicines Board) and the appropriate health ethics committee. It is important to note that a nurse and a physician will be immediately available (in less than 1 min) to manage any possible side effects during the study time.

An independent monitoring committee (ICS) of three experts has been constituted to analyze and classify the critical events and their possible link with opiates, especially death, respiratory depression, and uncontrollable vomiting that do not respond to treatment plans. A committee of three independent external expert investigators will be established. This committee will monitor the study and may be requested at any time by the sponsor to issue a written report on accountability in any SAE processing opinions or data appearing in the study that are likely to change the risk/benefit ratio of the research. The committee will meet at least once per year and whenever necessary upon request of the sponsor. Written reports of meetings of the expert committee will be forwarded to the sponsor and investigators. The annual safety reports will be given to each member.

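### Two participant-protection rules need correcting as printed: the 12-month limit in the menopause criterion runs against its purpose, and an all-French trial names an Irish authority for safety reports

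*Protocol article*

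**What the plan says.** **Eligibility.** Table 1, under Subject selection and inclusion criteria, has a block headed "For women (childbearing age". It holds three entries. The first is contraception, with three accepted methods named. The second, on menopause, reads "Menopausal status (amenorrhea less than 12 months before the inclusion visit". The third is sterility that has been established by a diagnosis or by surgery.

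The exclusion half of the same table separately lists "Pregnancy or lactation".

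**Safety reporting.** The section of that name makes the sponsor, a French university hospital, responsible for ensuring that "relevant and available information is forwarded to the competent authority (Irish Medicines Board", and also for informing the ethics committee. The Setting section describes the trial as "conducted in 10 French adult EDs in tertiary care academic hospitals". The section on randomization and allocation concealment places deferred consent under French law.

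**The concern.** Both statements are working rules rather than background. The first decides who may enter the trial; the second decides which regulator hears about harm.

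Contraception and sterility are on the list because each makes pregnancy unlikely or impossible. The menopause entry should do the same, but its 12-month limit points the other way. A recent absence of periods does not show that a woman cannot conceive, and it can itself be a sign of the pregnancy that the trial excludes. The criteria are checked in the emergency department before enrollment, and written consent may be deferred, so a reversed criterion copied into a screening form would be applied under time pressure.

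The named authority has no stated link to the trial. The route of administration under test is one that the Abstract says has not been adequately studied in adults, so where the sponsor sends safety information matters.

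**Working it through.** No arithmetic applies. The check is to set the statements side by side.

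**1. The menopause entry against its neighbours**

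| Entry | What it establishes, as printed |
|---|---|
| Contraception | Pregnancy is unlikely |
| Sterility, documented | Pregnancy is not possible |
| Menopause, with amenorrhea under 12 months | Only that periods have been absent for a short time |

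Two cases show the direction.

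- A woman two months without a period, using no contraception, meets the amenorrhea limit.
- A woman with 12 months or more does not meet it.

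The phrase can be read as amenorrhea that has lasted less than 12 months, or as amenorrhea that began less than 12 months before the visit. Both readings give the same direction, so the ambiguity does not rescue the entry.

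**2. The menopause entry against the exclusion list**

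Pregnancy is a stand-alone exclusion and applies whichever entry a woman meets. It limits what the wrong entry can cause. It does not make a short absence of periods a marker of inability to conceive, so the entry still fails at its own task.

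**3. The named authority against the rest of the article**

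| Element | Place in the article | Country |
|---|---|---|
| 10 emergency departments | Setting | France |
| Sponsor | Safety reporting | France |
| Law cited for consent | Randomization, allocation concealment | France |
| Competent authority | Safety reporting | Ireland |

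No Irish site, sponsor or partner appears anywhere in the article. The last row contradicts the other three.

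**4. How far the second error reaches**

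The reporting chain in Safety reporting has these steps:

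- adverse events are recorded on forms and in a log;
- they are reported to the sponsor;
- the sponsor informs the competent authority and the ethics committee;
- independent experts classify critical events, and the committee's members receive the annual safety reports.

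Only the sponsor's report to the authority carries the wrong name.

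**The case against.** The strongest reply is that these are two slips of wording whose effect is small. Much of it stands.

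- **The block is headed for women of childbearing age.** A reader might infer that the rule turns away women who cannot become pregnant, for example a woman ten years past menopause, and so misclassifies nearly all women who rely on menopause. The article does not support this. Such a woman can be read as outside the block altogether, and no count of affected women is given. What stands is narrower: for a woman to whom the block applies, 12 months or more of amenorrhea does not meet the printed definition.
- **Pregnancy is excluded separately, and the leading term of the entry is menopausal status.** A reader might infer that the trial enrolls pregnant women. The text does not show that. The amenorrhea wording qualifies the leading term, and the exclusion still operates. But the wording in brackets is the only definition of that term in the article, and it points the wrong way.
- **Only one name is wrong in the reporting chain.** A reader might infer that every serious event report from all 10 centres is misdirected. The centres report to the sponsor, and that step is stated correctly.
- **The same section also allows adverse event reports from a parent or guardian.** In an adult trial that excludes persons under guardianship this is idle text with no effect on what is captured. At most it suggests that wording was carried over from another protocol.
- **The article condenses a full protocol that is not shown.** Either error could be a translation or copying slip confined to the article. That is a reason to check the source documents. It does not make the published text right.

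**Conclusion.** The point holds in a limited form. The menopause entry in Table 1 is wrong as printed, because its 12-month limit defeats the purpose of the list it belongs to. The named competent authority contradicts the French sites, sponsor and legal framework.

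The size cannot be put in numbers. The first error concerns women of childbearing age who would qualify through the menopause entry, with the pregnancy exclusion as a remaining safeguard. The second concerns one step, the sponsor's report to the regulator. Neither touches the target of 850 patients, the 7% margin, the error rate or the primary analysis.

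The conclusion rests on two assumptions: that the three entries are alternatives meant to identify women unlikely or unable to become pregnant, and that the trial has no Irish involvement beyond what the article states. The article does not show that any ineligible woman was enrolled or that any report went to Ireland. Both errors deserve correction because they bear on participant protection: the article appeared in April 2019, with enrollment scheduled until 19 September 2019.

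**What to change.** 1. Reconcile the direction of the 12-month amenorrhea wording in Table 1 with the full protocol and with the purpose of the list.
2. Check the eligibility item in the eCRF against the reconciled wording. If the item carried the printed wording, review the women who qualified through that entry.
3. In Safety reporting, replace the named authority with the competent authority for a trial conducted in France.
4. Have the sponsor confirm where its safety reports have been sent since enrollment began on 19 September 2017.

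The cost is two text corrections and two checks, one of the eCRF and one of the sponsor's safety reporting. No design or analysis element changes. If the full protocol and the eCRF are already right, a correction to the article is enough.
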